### Study design and setting

A stepped-wedge controlled trial will be conducted in maternity services in three health sectors within the Hunter New England Local Health District, New South Wales, Australia. As shown in Fig. 1, measurement of the outcomes will occur continuously via telephone surveys with weekly random samples of pregnant women who have attended the maternity services in the last 2–3 weeks, from 6 months prior to the delivery of the intervention in the first sector to 12 months after intervention completion in the last sector. Delivery of the 4-month implementation intervention in the three sectors will occur sequentially. The sequential delivery will provide pre- and post-intervention outcome data periods of variable lengths for each sector, with a minimum of 12 months post-intervention data to enable the assessment of the sustainability of the intervention effect. Intervention effect will be determined by comparing the prevalence of recommended care between the pre-intervention and post-intervention periods for the three sectors combined.

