**Fig. 1 Fig1:**

Data collection and intervention timeline for the stepped-wedge trial design

The stepped-wedge study design provides pragmatic and scientific advantages relevant to the conduct of complex implementation interventions in health services [32, 45]. First, such a design provides the same level of evidence as a standard parallel cluster controlled trial [46]. Second, the design addresses the practical difficulty of recruiting enough equivalent maternity services that would be required for a parallel cluster RCT and increases study efficiency by using each group as its own control [32, 45]. Third, the design provides an opportunity for all participating services to receive the intervention, providing motivation for clinician engagement. Finally, such a design demonstrates the feasibility of the intervention in an operational environment, a key determinant of the intervention being translated into routine practice elsewhere should it prove successful [45].

In Australia, public maternity services are a key setting for the provision of antenatal care to address gestational weight gain as they provide care for 55% of all birthing women, including care for a diverse range of population groups, including those with a high prevalence of risk and those who are disadvantaged [47, 48]. The maternity services involved in this trial provide care to approximately 7000 women annually across urban and rural areas, accounting for almost 70% of women birthing in public hospitals within the health district [46].

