#### Pregnant women

All pregnant women who attend participating services from the start of the implementation intervention in their sector will receive the recommended model of gestational weight gain care. During the 30-month data collection period, women who have had an antenatal appointment at any of three time points: (i) the first public antenatal clinic appointment, (ii) 27–28 weeks gestation, or (iii) 35–36 weeks gestation, will be eligible to participate in the data collection surveys. Eligibility for participation in such surveys will require women to be aged 18 years or older, be pregnant at more than 12 weeks gestation and less than 37 weeks gestation, have a sufficient level of English language proficiency to complete the survey unaided, and be mentally and physically capable of completing the survey. Women will be ineligible to participate in the data collection surveys if they are determined by a maternity service clinician to be inappropriate to contact for the survey (e.g. due to medical or social issues), are seeing a private provider as the primary provider of their antenatal care, have given birth or had a negative pregnancy outcome, had already been selected to participate in the survey for that time point in the past 4 weeks, and/or had previously declined participation in the survey. Characteristics of women deemed ineligible will be recorded and reported.

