### Sample size and power calculations

Based on recruitment outcomes of previous trials conducted by the research team in clinical settings and maternity services specifically, it is expected that 70% of invited women, or 15 women (average of 5 per service), will consent to participate in weekly surveys for each of the three time periods (‘first appointment’, ‘27–28 weeks gestation’, or ‘35–36 weeks gestation) (total *N* = 45 per week) [70]. This will yield 5600 data points over the course of the data collection period, sufficient to detect (with 80% power and with a Bonferroni adjusted alpha of 0.0167) for the primary outcomes a (1) 15% absolute increase in receipt of recommended assessment of gestational weight gain (baseline prevalence estimate of 40%), (2) 14% absolute increase in recommended advice (baseline prevalence estimate of 30%), and (3) 9% absolute increase in the offer of recommended referral (baseline prevalence estimate of 10%).

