### Statistical analysis

Pre- and post-intervention primary outcome data will be analysed using mixed effects logistic regression models to detect a change in the reported receipt of each of the three elements of the best practice care pathway for addressing gestational weight gain (assessment, advice, and referral) for all three sectors combined. Separate models will be fitted for each outcome. The main predictor of interest will be a before/after intervention indicator variable as well as a fixed effect for time, and a random intercept for an antenatal time point (first appointment, ‘27–28 weeks gestation’, or ‘35–36 weeks gestation’). The implementation intervention will be declared effective if the coefficient for the intervention period variable is below the threshold of *α* = 0.0167 for any of the three primary outcomes. A time-series analysis will be performed over the post-intervention periods to determine if slope changes occur, as an indicator of sustainability. Pre- and post-intervention secondary outcome data will be analysed using mixed effects logistic regression models to detect a change in each outcome for all three sectors combined. Descriptive statistics will be used to report on the process measures. The cost analysis and practice change cost-effectiveness results will be incorporated into an economic model to project the expected costs and outcomes that would be associated with broader scale-up of the implementation intervention to antenatal services across the state. SAS (V9.3 or later) will be used for all statistical analyses.

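### The primary model as listed has no term for sector, the unit across which the intervention is stepped, so stable sector differences are partly confounded with the intervention effect

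*Protocol article*

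**What the plan says.** In the protocol article, Statistical analysis, each primary outcome gets a mixed effects logistic model fitted "for all three sectors combined". The listed terms are "a before/after intervention indicator variable as well as a fixed effect for time, and a random intercept for an antenatal time point". Antenatal time point is the type of visit (three levels). No fixed or random term for sector or service is named. The success rule reads "The implementation intervention will be declared effective if the coefficient for the intervention period variable is below the threshold of" 0.0167, for any one of the three primary outcomes.

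Study design and setting says that a 4-month intervention is delivered to three sectors one after another, and that the effect is found by "comparing the prevalence of recommended care between the pre-intervention and post-intervention periods for the three sectors combined". The same section argues that the stepped-wedge design "increases study efficiency by using each group as its own control". The Usual care paragraph expects care before the intervention to differ between maternity services and clinicians.

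Sample size and power calculations states "This will yield 5600 data points over the course of the data collection period", sufficient to detect increases from 40% by 15 points, from 30% by 14 and from 10% by 9, "with 80% power and with a Bonferroni adjusted alpha of 0.0167". It gives no intracluster correlation (ICC) or between-sector variance.

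**The concern.** The before/after indicator switches at a different date in each sector, so being exposed is associated with which sector a woman attends. A model with a sector term compares each sector with itself over time. A model without one also compares sectors with each other, and any lasting difference in usual care between early and late sectors enters the intervention coefficient. The random intercept for visit type does not help, because visit type is not the unit that is stepped.

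An SAP might add a sector term. The article, however, does not leave the structure open: it names the fixed and the random terms, and sector is not among them. That conflicts with its own reason for choosing the design. At stake are the primary estimate and the 0.0167 threshold on which the trial's conclusion rests.

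**Working it through.** **The plan's own figures.** Alpha: 0.05/3 = 0.0167, reproduced. Data points: 45 per week x 130 weeks = 5850, against 5600 stated. Power: a plain two-proportion comparison needs only 462, 496 and 638 women in total for the three outcomes, so 5600 would give close to 100%. The listed model (no sector), with month categories and implementation months dropped, gives 83/80/66%. No variant tried gives 80% for all three. Because the article does not state its method or ICC, the power claim is not reproducible rather than shown to be wrong.

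**Layout.** The window is 6 + 3 x 4 + 12 = 30 months. Dropping each sector's implementation months:

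| Sector | Pre months | Post months | Share of pre data | Share of post data |
|---|---|---|---|---|
| 1 | 1-6 (6) | 11-30 (20) | 6/30 = 20% | 20/48 = 42% |
| 2 | 1-10 (10) | 15-30 (16) | 10/30 = 33% | 16/48 = 33% |
| 3 | 1-14 (14) | 19-30 (12) | 14/30 = 47% | 12/48 = 25% |

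**False effect with no true effect** (least squares on prevalence, equal numbers per sector-month). Take assumed sector prevalences of 50/40/30%.

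- No time term: post mean 0.417 x 50 + 0.333 x 40 + 0.25 x 30 = 41.7; pre mean 0.20 x 50 + 0.333 x 40 + 0.467 x 30 = 37.3; difference +4.3 points.
- Linear time: regress the indicator on month and keep the residuals. Their sums are +3.264, 0 and -3.264 in sectors 1, 2 and 3, and their sum of squares is 4.761. The false effect is 3.264/4.761 = 0.686 times the sector 1 minus sector 3 gap: 0.686 x 20 = 13.7 points.
- Month categories: only months 11-14 contain both an exposed and an unexposed sector (sector 1 post, sector 3 pre), so the multiplier is 1 and the result is +20.0 points.

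| Gap, sector 1 minus sector 3 | Linear time | Month categories |
|---|---|---|
| 0 (e.g. 40/30/40) | 0 | 0 |
| 4 (42/40/38) | 2.7 | 4.0 |
| 10 (45/40/35) | 6.9 | 10.0 |
| 20 (50/40/30) | 13.7 | 20.0 |

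Signs reverse if the order reverses. With sector fixed effects every entry is zero.

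**Type I error.** Simulated under no effect: 1000 trials per setting, two-sided 0.0167, 5600 points over 30 months, implementation months dropped, visit type fitted as fixed in place of its random intercept. Between-sector SD on the logit scale is assumed; ICC = SD^2/(SD^2 + pi^2/3). Ranges cover the three baselines and both codings of time.

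| SD | ICC | No sector term |
|---|---|---|
| 0 | 0 | 1.3-2.4% |
| 0.1 | 0.003 | 2.1-6.7% |
| 0.2 | 0.012 | 8.6-22.6% |
| 0.3 | 0.027 | 16-34% |
| 0.5 | 0.07 | 34-55% |

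With sector fixed effects the error is 1.0-2.7% at every SD in the table. With added sector-by-month variation (SD 0.2, sector SD 0.3) it is 36% without sector and 5.6% with it.

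**Price of the sector term** (month categories, implementation months dropped). Standard error for the assessment outcome: 4.4 to 4.8 points, a ratio of about 1.10. Power for assessment/advice/referral:

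| 5600 points cover | Without sector | With sector |
|---|---|---|
| all 30 months | 83/80/66% | 74/71/58% |
| pre and post months only | 88/86/73% | 81/78/65% |

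With linear time, power with sector stays at about 97% or more.

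**The case against.** The strongest reply is that the harm depends on a quantity the article does not give. If sectors do not differ, the listed model has nominal error; if sectors 1 and 3 are equal, the estimate is unbiased whatever sector 2 does. The confounding is only partial, since every sector supplies data before and after. The article does not say how the order was chosen. If it was random, the estimate would be unbiased on average over orders, although its standard error would still be too small. All of this stands, and it is why the size is given as a range starting at zero.

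Three stronger readings are tempting and not supported.

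- A reader might infer that the error rate is far above 1.67% as a matter of fact. That needs a between-sector variance. The Usual care paragraph makes zero variation implausible but supplies no figure.
- A reader might infer that the coefficient simply is the sector 1 minus sector 3 difference. That holds for month categories only. The article does not fix the coding of time, and with linear time the multiplier is 0.69.
- A reader might infer that repeat surveys of one woman are a further serious fault, since re-selection is barred only if she "had already been selected to participate in the survey for that time point in the past 4 weeks". The article gives no repeat rate. A rough figure: 7000 women a year is about 135 a week per time point; 15/135 = 11%; two other time points give about 0.22 further surveys per respondent; at an assumed within-woman ICC of 0.3 the design effect is 1 + 0.22 x 0.3 = 1.07. That is too small to add to this point.

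**Conclusion.** The point holds. The primary model, as the article lists it, omits the unit across which the intervention is stepped and contradicts the article's own rationale for the design. Any stable difference between the first and last sectors is passed into the intervention effect, at about 0.69 of its size with linear time and in full with month categories. Against target effects of 9 to 15 points, a 10-point gap in roll-out order would yield a false effect of 7 to 10 points. The type I error ranges from nominal at zero between-sector variance to about 34-55% at ICC 0.07. These figures rest on the 30-month layout with implementation months dropped, even recruitment, a two-sided test and an assumed between-sector variance. Because the defect lies in the primary analysis and its success rule, it should be corrected before analysis.

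**What to change.** In Statistical analysis, add sector as a fixed effect with three levels to each primary model, and do the same in the secondary outcome models. Three sectors are too few for a reliable random effect. This removes the bias from stable sector differences and brings type I error to about 1-3% when there is no sector-by-month variation. A random intercept for service by month is an optional addition if such variation is expected. The rest of the listed model can stay as it is.

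Data collection does not change, but precision is lost: the standard error rises by about 10%. With month categories, implementation months dropped and 5600 points over all 30 months, power falls from about 83/80/66% to 74/71/58% for assessment, advice and referral. The 80% power statement in Sample size and power calculations should therefore be restated under the corrected model, giving the coding of time, the handling of the implementation months and the between-sector variation assumed.

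### The only effectiveness rule names the coefficient where a p-value is evidently meant, and it requires no direction of effect

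*Protocol article*

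**What the plan says.** The protocol article states its decision rule once, in Statistical analysis. The intervention "will be declared effective if the coefficient for the intervention period variable is below the threshold of" α = 0.0167, and this need hold only "for any of the three primary outcomes".

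The same section fixes the scale of that coefficient: "Pre- and post-intervention primary outcome data will be analysed using mixed effects logistic regression models to detect a change" in each care element. It also names the term: "The main predictor of interest will be a before/after intervention indicator variable". How the indicator is coded is not stated.

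The figure 0.0167 appears in one other place, Sample size and power calculations, where the planned data are called "sufficient to detect (with 80% power and with a Bonferroni adjusted alpha of 0.0167) for the primary outcomes" of three absolute increases: 15 points from 40% (assessment), 14 points from 30% (advice) and 9 points from 10% (offer of referral). Whether the test is one- or two-sided is not stated.

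The Aim section defines effectiveness as raising the delivery of recommended care.

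**The concern.** Two things are wrong with the sentence, and they are separate.

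1. **Quantity.** A log odds ratio is compared with a significance level. These are different kinds of number, and a coefficient being below 0.0167 says nothing about evidence for an effect.
2. **Direction.** Nothing in the rule asks for an increase. The models are set up to detect a change of either sign, and the rule does not narrow that. This gap remains after p-value is substituted for coefficient.

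This sentence is the article's only criterion for calling the intervention effective, and the Discussion part of the Abstract ties wider scale-up to that conclusion. The direction matters most when the three outcomes disagree, for example if one falls and two stay flat. In that case the written rule has to give a clear answer, and it does not give the right one.

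**Working it through.** **Inputs.** From Sample size and power calculations: baselines 40%, 30% and 10%; increases 15, 14 and 9 points; power 80%; alpha 0.0167. From Statistical analysis: logistic models, and a rule met by any one of three outcomes. Assumptions of this check: indicator coded before = 0, after = 1; two-sided test; normal approximation.

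**Step 1. Reproduce the threshold.** 0.05/3 = 0.01667, which rounds to 0.0167. The figure is a Bonferroni share of 5%, so it is a significance level.

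**Step 2. The coefficient at each target.** Log odds ratio = ln{[p2/(1 − p2)] / [p1/(1 − p1)]}.

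- Assessment, 40% to 55%: (0.55/0.45)/(0.40/0.60) = 1.833; ln = 0.606.
- Advice, 30% to 44%: (0.44/0.56)/(0.30/0.70) = 1.833; ln = 0.606.
- Referral, 10% to 19%: (0.19/0.81)/(0.10/0.90) = 2.111; ln = 0.747.

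All three exceed 0.0167, so all three fail the literal rule. A coefficient of 0, or any negative coefficient, passes it. A coefficient of exactly 0.0167 is a rise of only 0.40, 0.35 and 0.15 percentage points from the three baselines.

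**Step 3. How the literal rule would behave.** Take the standard error implied by the stated power: SE = log OR/(2.393 + 0.842). This gives 0.606/3.235 = 0.187 for assessment and advice, and 0.747/3.235 = 0.231 for referral.

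- No effect: Φ(0.0167/0.187) = 0.54, 0.54 again for advice, and Φ(0.0167/0.231) = 0.53. For any of three, if independent, about 0.90.
- Target effect: Φ((0.0167 − 0.606)/0.187) = 0.0008, with 0.0008 for each of the others. For any of three, if independent, about 0.002.

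With reverse coding (before = 1, after = 0) an increase has a negative coefficient and would pass, but a coefficient of 0 would still pass. Neither coding makes the literal rule valid.

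**Step 4. Read as a p-value, with no sign required.** Hold the same SEs and take a fall of the same log-odds size as each target. The after-period odds are:

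- Assessment: 0.6667/1.833 = 0.364, or 26.7% (from 40%).
- Advice: 0.4286/1.833 = 0.234, or 18.9% (from 30%).
- Referral: 0.1111/2.111 = 0.0526, or 5.0% (from 10%).

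The probability of significance is Φ(3.235 − 2.393) = Φ(0.842) = 0.80 per outcome, the same as for the targeted rise. Under the rule so read, each such result meets the criterion.

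**Step 5. Read as a p-value, with odds ratio above 1 required.** Each target still passes with the planned 80%. A true null passes with probability 0.0167/2 = 0.0083 per outcome, at most 3 × 0.0083 = 0.025 over the three. A fall of the size in step 4 has essentially no chance of passing.

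**The case against.** The strongest reply is that this is a slip of the pen. The sentence compares the coefficient with α, not with a bare number, and the sample size section says what that α is: "with 80% power and with a Bonferroni adjusted alpha of 0.0167". The only coherent reading is that the test of the coefficient must be significant at 0.0167. That stands. A reader might infer from steps 2 and 3 that the trial will call its own target effects failures, or reach a conclusion opposite to its data. The document does not support that: it points to a p-value, and the literal result also depends on a coding that is not stated.

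The second reply is that direction is supplied elsewhere. The aim is to raise care and every powered effect is an increase, so a fall could hardly be called effective; a two-sided test with direction read from the estimate is ordinary practice, and sidedness is often left to the analysis plan. This carries weight as to what was intended. It does not repair the rule, because the article does not leave the rule to another document: it states one, and that rule, even with p-value substituted, is met by a significant fall. A later plan that states the rule correctly would contradict this text.

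Two further inferences should not be drawn. One is that half of each 0.0167 is wasted on harm. Sidedness is not stated, and the correction below keeps a two-sided test, so the split of alpha does not change. The other is that success on one outcome while the other two do not move is itself a fault. Any-of-three with a Bonferroni share is a valid prespecified rule, and it is kept.

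**Conclusion.** The point holds as a wording error in the article's sole decision rule. As written, the rule compares a log odds ratio with a significance level, and no other section states it correctly. The intended quantity is clear from the sample size section, so the literal consequences show why the sentence cannot stand; they do not predict what an analyst would do. They rest on the assumed before = 0, after = 1 coding.

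The missing direction does not depend on that coding. Under the p-value reading, a fall as large in log-odds terms as a target would meet the rule about 80% of the time for that outcome, assuming a two-sided test and the standard errors implied by the stated power. This conflicts with the Aim section and with the powered increases. The design, the model and the multiplicity adjustment are not called into question by this point.

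**What to change.** Replace the sentence with wording such as: the intervention is declared effective if, for at least one primary outcome, the two-sided p-value for the intervention coefficient is below 0.0167 and the after-versus-before odds ratio is above 1; any significant decrease in a primary outcome is reported alongside the conclusion.

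Stating the odds ratio as after versus before also removes the dependence on how the indicator is coded.

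The cost is one sentence. The sample size, the power at the three targets and the any-of-three Bonferroni structure do not change. The route for the correction is already described under Trial discontinuation or modification, which commits to updating the registration record when the protocol is modified.

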In addition, no studies have tested the effect of practice change strategies to enhance all elements of antenatal guideline care for gestational weight gain, that is, assessment of weight, provision of advice, and referral to support services [41]. Most existing studies have examined the effect of strategies on routine weight assessment only, provision of advice for gestational weight gain only, or both assessment and advice. For example, an Australian cohort study (*N* = 13,000 pregnancies) found that recording of weight improved through the provision of weighing scales and staff training (18.9%) and medical record prompts (61.8%) (*p* < 0.01) [41]. A U.S. cohort study of 733 clinicians that introduced medical record prompts also demonstrated an increase in recording of weight (*p* < 0.001) and GWG counselling (*p* < 0.001) [42].

Similarly, despite intervention cost-effectiveness and budget impact being a significant factor in health care decision-making [43], no economic evaluations of such implementation interventions have been reported [44]. Given these evidence gaps, a need and opportunity exist for rigorous trials to examine the effectiveness, efficiency, and affordability of implementation interventions designed to increase the provision of recommended antenatal care addressing gestational weight gain.

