### Aim

The aim of this study is to determine the effectiveness of an implementation intervention in increasing the provision of recommended gestational weight gain care in antenatal appointments.

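### One passing element out of three labels the whole intervention effective, which is broader than that result supports; Holm with element-named conclusions fits better at the same 5% error rate

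*Protocol article*

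**What the plan says.** All of this is in the protocol article.

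- **Statistical analysis.** "Separate models will be fitted for each outcome", and there are three primary outcomes: assessment, advice and offer of referral. One verdict on the intervention follows if the intervention-period coefficient is "below the threshold of *α* = 0.0167 for any of the three primary outcomes". No step-down or ordered procedure is described.
- **Sample size and power calculations.** Each outcome is sized "with 80% power and with a Bonferroni adjusted alpha of 0.0167", with its own detectable increase: 40% to 55% for assessment, 30% to 44% for advice, 10% to 19% for referral.
- **Aim.** The trial is to determine the "effectiveness of an implementation intervention in increasing the provision of recommended gestational weight gain care in antenatal appointments".
- **Background.** The gap is described thus: "no studies have tested the effect of practice change strategies to enhance all elements of antenatal guideline care for gestational weight gain". Most earlier work is said to have looked at assessment only, advice only, or those two.
- **Secondary trial outcomes.** Receipt of every element of the pathway is a secondary outcome and plays no part in the effectiveness rule.

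**The concern.** Three tests at 0.0167 support two kinds of statement: that at least one element changed, and that each particular element which passed changed. The rule turns any such result into one verdict on the intervention as a whole. If only weighing improved, with advice and referral unchanged, the prespecified conclusion would still be that the intervention is effective, with no requirement to say for what. The abstract's Discussion ties possible application at scale to a demonstration of effectiveness, so the wording of that conclusion matters.

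The second matter is separate. Under single-step Bonferroni each element faces 0.0167 even after another has been rejected. Holm's step-down procedure relaxes the later thresholds to 0.025 and 0.05, controls the same family-wise rate, and never rejects less. If conclusions are to be stated element by element, element-level power is what counts.

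**Working it through.** **1. The plan's alpha.** 0.05 / 3 = 0.016667, which rounds to the stated 0.0167. If the three tests are independent and no effect exists, the chance of at least one rejection is 1 − (1 − 0.0167)³ = 0.0493. Positive correlation lowers it (table below). The type I error of the rule is sound.

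**2. Inputs for the comparison.**
- From the document: three outcomes, alpha 0.0167 each, 80% power each.
- Assumed: two-sided tests (the article does not state sidedness), and correlations of 0, 0.3, 0.5 and 0.8 between the three test statistics (the article gives none).
- The 80% is taken as stated. Simple two-sample formulas would need only 462, 496 and 638 women in total for the three effects, against 5600 data points. The planned figure must therefore include a design allowance that is not shown. The comparison below needs only the 80%, not how it was reached.

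**3. Standardised effect.** z(1 − 0.05/6) + z(0.80) = 2.394 + 0.842 = 3.236. At that effect, an element passes 0.0167 with probability 0.80, 0.025 with about 0.84, and 0.05 with about 0.90 (0.899).

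**4. Closed-form check with independent tests and all three effects real.** Split each p-value into A (at or below 0.0167), probability 0.80; B (0.0167 to 0.025), 0.040; C (0.025 to 0.05), 0.059.
- An element in A is always rejected by Holm: 0.800.
- An element in B is rejected if at least one other is in A: 0.040 × (1 − 0.2²) = 0.038.
- An element in C is rejected if the other two are both in A, or one in A and one in B: 0.059 × (0.8² + 2 × 0.8 × 0.040) = 0.059 × 0.704 = 0.042.
- Sum: 0.800 + 0.038 + 0.042 = 0.880, against 0.800 under Bonferroni.
- At least one success, either method: 1 − 0.2³ = 0.992.

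**5. Simulation (1,000,000 draws of three correlated z-statistics).** The row for correlation 0 agrees with step 4.

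| Correlation | Family-wise error, no effects (both methods) | Power per real element, Bonferroni → Holm: three real | Two real | One real | At least one success, three real (both methods) |
|---|---|---|---|---|---|
| 0 | 4.9% | 80% → 88% | 80% → 83% | 80% → 80% | 99% |
| 0.3 | 4.8% | 80% → 87% | 80% → 83% | 80% → 80% | 97% |
| 0.5 | 4.5% | 80% → 86% | 80% → 83% | 80% → 80% | 95% |
| 0.8 | 3.5% | 80% → 85% | 80% → 82% | 80% → 80% | 90% |

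The chance that all three elements pass when all three effects are real rises from 51%, 57%, 61% and 69% to 72%, 74%, 77% and 81% in the same order.

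**6. The global label.** If exactly one element truly improves by its planned amount, the rule calls the whole intervention effective about 81% of the time. For independent tests this is 1 − 0.2 × (1 − 0.0167)² = 0.807. If all three improve as planned, exactly one passes 0.0167 in about 9–11% of trials. Holm does not change how often the any-of-three rule is met, so it does not by itself narrow the conclusion. That needs a change of wording.

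**The case against.** Much of the defence stands. An at-least-one rule with Bonferroni is a standard, prespecified choice, and it agrees with the sample-size section. No promised power is lost, because the 80% was set at 0.0167. The 81% above is not an error rate; it is essentially the planned power to detect one true improvement. Each element has its own model and so its own result, and receipt of every element is a secondary outcome in which a weighing-only effect would show itself. The cost-effectiveness and scale-up work does not run on a yes/no label. Holm's gain needs more than one real effect and is almost nil when only one element improves.

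A reader might infer more than this, in two ways. The first is that the rule inflates the false-positive rate; step 1 shows that it does not. The second is that the aim and the Background require all three elements to pass before any overall claim. They do not say so. The Aim speaks of recommended care without making success joint, and the Background remark says what earlier studies left untested, not what counts as success here. Requiring all three is a judgement call with a real price: at the planned effects, power for the overall claim would fall from 90–99% (any element) to 72–81% (all three, by Holm).

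What the defence does not remove is that the stated conclusion names the intervention and not the element, and that a uniformly more powerful procedure is available at the same error rate.

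**Conclusion.** The point holds as a recommended improvement, not as an error. The rule is valid and controls the family-wise error at 5%, but its single label is broader than a one-element result supports. Single-step Bonferroni also leaves element-level power unused: about 5–8 percentage points per element if all three effects are real, 2–3 if two are, and practically none if one is. These figures assume two-sided tests, effects exactly at the size giving 80% power at 0.0167, and equal correlations between 0 and 0.8. The document does not support a demand that all three elements pass before any overall claim.

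**What to change.** In the Statistical analysis section, replace the effectiveness rule with wording such as:

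> The three two-sided primary p-values will be tested by Holm's step-down procedure (smallest against 0.0167, next against 0.025, largest against 0.05, stopping at the first that fails), with family-wise alpha 0.05. Effectiveness will be declared for each element that passes and shows an increase, and the conclusion will name the element or elements improved.

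This also makes plain that p-values are compared with alpha; the present sentence literally compares a coefficient and gives no direction. The sample-size section can stay as it is, since 80% at 0.0167 is a lower bound on the power under Holm at the same effects.

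The cost is a few sentences and an update of the trial registration, best made before outcome data are analysed; no extra data are needed. The headline is narrower when only one or two elements improve. Simultaneous confidence intervals matching Holm are less simple. Intervals at 98.33% can still be shown, but one may include no effect for an element that Holm rejects at 0.025 or 0.05.
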